**Flow Diagram RCT.**

### Inclusion and exclusion

The inclusion criteria are:Age 18 or older;Fluent in Dutch speaking and reading abilities (clinical observation by RA1) and;A primary DSM-IV-TR diagnosis of alcohol dependence or abuse.

This last criterion is assessed during the regular intake procedure by a health care or clinical psychologist.

Exclusion criteria are:Meeting the DSM-IV-TR criteria for current PTSD;Meeting the DSM-IV-TR criteria for current dependence and regular (at least once per week in the last 2 weeks before eligibility screening) use of substances other than alcohol or nicotine;Current (in the last two weeks before eligibility screening) regular alcohol use (at least > 21E (women) or > 28E (men) per week) and;Severe, current (since the start of regular treatment) psychiatric symptoms (especially manic, psychotic, suicidal and aggressive symptoms) that interfere with TAU.

These criteria are assessed during intake by a health care or clinical psychologist and/or (re)assessed by RA1 during screening. RA1 uses segments of the Mini-International Neuropsychiatric Interview-Plus (MINI-Plus [43]), the Measurements in the Addictions for Triage and Evaluation (MATE 2.1 [44]) and/or clinical observation as well as information from the patients dossier.

When RA1 detects psychopathology not detected during regular intake, the participant is informed as well as his/her regular therapist to ensure further diagnostics and treatment is provided, if necessary.

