### Power and sample size calculation

Since two active treatment arms are compared and the sample is expected to be relatively heterogeneous regarding baseline variables such as dependence severity, drinking status and other substance use, it is estimated that the effect size will be relatively small. Clinical relevant differences on the primary outcome variable (changes in number of heavy drinking days in the previous 30 days) were calculated on the basis of data of a recent study [46]. In patients with an alcohol-use disorder referred to in- or outpatient alcohol treatment the mean baseline score for heavy drinking days (≥5 drinks in a single day, over the past 30 days) was 16.33 (SD 11.99). Treatment outcome was such that undertreated patients (<75% attendance of the number of sessions recommended by treatment allocation guidelines, n = 618) showed a reduction of 8.7 heavy drinking days (±12.5) while overtreated patients (>110% attendance of sessions recommended) showed a reduction of 12.5 heavy drinking days (±12.2, n = 362). The difference between under- and overtreated patients is at least 3.8 heavy drinking days over the past 30 days which corresponds to an effect size of *d* = 0.31 or *f* = 0.15).

Subsequent poweranalysis in G*Power version 3.1.2. [47] (ANOVA: repeated measures, within-between interaction) indicated a sample size of 74 to demonstrate this effect (keeping α at 0.05 and power at 0.80 and using 2 groups and 3 measurements (concerning changes in the number of heavy drinking days between 4 time points)). Attrition is estimated to be relatively high at 33%. Therefore we add 26 participants (100 patients in total, 50 in each treatment arm), to meet the required sample size.

To minimize missing values RA1 will use email, text messages, telephone calls, and/or contacts with participants’ regular therapists to remind participants about their assessment appointments. All participants will receive financial compensation of 25 euros (in the form of a gift cheque) for every complete assessment at T2 and T3, regardless of whether or not the participant drops out of treatment.

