### Interventions

#### Treatment as usual (TAU)

All participants already receive TAU at the moment they are enrolled and will continue to receive TAU for as long as indicated by their regular therapists but at least until T1. TAU may differ in intensity or additional components delivered (e.g. family treatment) between participants. In IrisZorg, most out-patients of care pathway ‘youth’ and ‘addiction’ receive (Adolescent) Community Reinforcement Approach ((A)CRA) treatment, consisting of several interventions, based on behavioral therapy principles [48]. Elements may include: functional analysis, training communication and/or problem-solving skills, sobriety sampling, social networking, learning to refuse substances, increasing alternative reinforcing activities, relapse management and medication monitoring. Treatment is individual but may also be partly groupwise. Patients receive TAU on a weekly basis by a health care worker.

Alternatively, some patients in care pathway ‘young’ may receive an intensive family treatment for youngsters up to 20 years old (and their families), who still live at home (or intend to go back to live at home again) and where multiple life domains may be affected (e.g. family, school, mental health, criminal behavior etc.): Multidimensional Family Therapy (MDFT [49]). Patients of care pathway ‘addition, care and housing’ receive Function Assertive Community Treatment (FACT [50]), a multidisciplinary, outreaching approach aimed at stabilization, treatment and recovery.

TAU is supervised by a clinical psychologist or psychiatrist. If necessary, treatment may be supplemented with medical care (such as, but not limited to medication), individual psychological care or relationship or family therapy. Incidentally or periodically, additional in-patient treatment may be necessary. CRA and MDFT typically lasts 6 months (in some cases CRA may be limited to 3 or extended to 9 months) while FACT may endure much longer.

‘Time-in-treatment’ before intervention and during the course of the study as well as main components and treatment intensity of TAU will be registered. The use of psychofarmaca, craving reducing (acamprosate, naltrexone) or abstinence enforcing medication (disulfuram) will be monitored.

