### Analyses

All analyses will be executed using SPSS. Summary tables will be provided for all baseline, end of treatment and follow-up variables. Data will be summarised using frequency tables (with confidence intervals when applicable), and descriptive statistics (mean, median, interquartile range, number and percentages of participants and two-sided, 95% confidence intervals when appropriate).

Changes in the number of heavy drinking days in the past 30 days will be used to analyze the efficacy and effectiveness of EMDR. Since this primary outcome variable is continuous, a repeated measures ANOVA will be carried out with 2 group (EMDR + TAU versus TAU) and 4 time (pre-, post-treatment, 1 and 6 month follow-up) factors. Randomization stratum will be used as a covariate. Effect sizes will be calculated.

All allocated participants will be included in the primary analysis (intention-to-treat, ITT). Since an ideal ITT requires a complete set of data [89], multiple imputation (or a similar strategy) will be used for missing data, if possible. In addition a per-protocol (PP or completers) analysis will be done. ITT analyses will provide insight into the effectiveness of the treatment in real life whereas PP analysis gives insight into the efficacy or the ability for the treatment to reach its intended effect under ideal circumstances.

Repeated measures of continuous secondary variables such as time to first alcohol consumption, number of total drinks consumed and average drinks per occasion in the past 30 days, severity of the dependence, level of rumination, negative affect, desire thinking, craving, coping self-efficacy, quality of life, biomarkers will be analyzed by carrying out a repeated measures ANOVA with 2 group (EMDR + TAU versus TAU) and 3 (post treatment versus 1 versus 6 month follow-up: time to first drink variable derived from TLFB data) or 4 time (pre- versus post-treatment versus 1 versus 6 month follow-up: all other data) factors.

Distribution of premature treatment termination (PTT), a categorical variable, will be analysed using chi-square tests. A range of baseline clinical characteristics potentially associated with subsequent PTT will be examined. A logistic regression analysis will be conducted to examine the relative contribution of key variables to PTT status. A Kaplan–Meier survival curve will be used to illustrate the distribution of PTT prior to the completion threshold at session 5.

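### The target of 74 patients comes from a change-score effect size entered as an interaction effect; on the article's own SDs, power for 3.8 days is far below the stated 80%

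*Protocol article*

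**What the plan says.** Under Power and sample size calculation, the article takes from a cited study a reduction of 8.7 heavy drinking days (SD 12.5, n = 618) in undertreated patients and 12.5 days (SD 12.2, n = 362) in overtreated patients. It concludes: "The difference between under- and overtreated patients is at least 3.8 heavy drinking days over the past 30 days". It equates this with d = 0.31 or f = 0.15. The baseline SD in that study is given as 11.99.

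It then names the G*Power procedure ("ANOVA: repeated measures, within-between interaction"), run at the 5% level for 80% power. The remaining setting is given as "using 2 groups and 3 measurements (concerning changes in the number of heavy drinking days between 4 time points". This "indicated a sample size of 74 to demonstrate this effect". With 33% attrition expected, 26 patients are added to reach 100.

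Under Analyses, the test to be powered is a 2 group × 4 time model: "Since this primary outcome variable is continuous, a repeated measures ANOVA will be carried out".

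**The concern.** The SDs of 12.5 and 12.2 are SDs of reductions, so d = 3.8 divided by about 12.4 is a standardised difference in a single change score, and f = d/2 is the matching between-group f. The within-between interaction procedure asks for something else: the SD of the group-by-time cell effects over the SD of one measurement. It then multiplies by 1/(1 − ρ) to credit the within-person correlation. The change SD already contains that correlation, so entering the change-score f credits it a second time, on top of using an f of the wrong kind.

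The 80% power for 3.8 days is the only justification offered for enrolling 100 patients. The Discussion says that even a relatively small effect may matter. If the real power for the stated target is a quarter to a third, a non-significant result would say little about whether that target effect exists, and a reader relying on the stated 80% could draw the wrong conclusion.

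**Working it through.** **Inputs from the article.** Difference 3.8 days; change SDs 12.5 (n = 618) and 12.2 (n = 362); baseline SD 11.99; α 0.05; power 0.80; 2 groups; 3 measurements entered; 4 time points analysed; 100 enrolled; 33% attrition, so 100 × 0.67 = 67 completers. **Assumed, because not stated:** correlation ρ = 0.5, compound symmetry, equal SDs over time.

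**1. Effect size.** Pooled change SD = √[(617 × 12.5² + 361 × 12.2²)/978] = 12.39. So d = 3.8/12.39 = 0.307 and f = d/2 = 0.153. The article's 0.31 and 0.15 are confirmed as change-score quantities.

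**2. Reproducing 74.** The G*Power interaction formula is λ = f²·N·m/(1 − ρ), with df = (m − 1) and (N − 2)(m − 1). With f = 0.15, m = 3, ρ = 0.5 and N = 74: λ = 0.0225 × 74 × 3/0.5 = 9.99, df 2 and 144, power 0.806. N = 72 gives 0.795, so 74 is the first balanced total to reach 80%. Other ways of using f = 0.15 come nowhere near 74: the between-factors option needs 236, and the alternative effect-size definitions (SPSS, Cohen) need 216 to 218.

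**3. The interaction f that 3.8 days implies.** For two equal groups with between-group differences δⱼ at m times, f = √[Σ(δⱼ − δ̄)²/(4m)]/σ, with σ = 11.99.
- Four levels (0, 3.8, 3.8, 3.8): δ̄ = 2.85, sum of squares 10.83, f = √(10.83/16)/11.99 = 0.069.
- Three levels (0, 3.8, 3.8): sum of squares 9.63, f = √(9.63/12)/11.99 = 0.075.

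The overstatement of λ at m = 3 is (0.15/0.075)², about fourfold. Of this procedure's multiplier m/(1 − ρ), only 1/(1 − ρ) = 2 is the correlation credit; m belongs to the definition of λ.

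**4. Power of the planned 2 × 4 test for 3.8 days.** λ = (N/4) × 10.83/[11.99² × (1 − ρ)], df 3 and 3(N − 2). With ρ = 0.5:

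| N analysed | λ | power |
|---|---|---|
| 67 | 2.52 | 23% |
| 74 | 2.79 | 25% |
| 100 | 3.77 | 33% |

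The article's own SDs imply ρ = 1 − 12.39²/(2 × 11.99²) = 0.47, which is slightly less favourable than 0.5.

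**5. Sensitivity, one assumption at a time.**
- ρ from 0.3 to 0.7, persistent difference: 17 to 37% (N = 67), 19 to 41% (N = 74), 25 to 53% (N = 100).
- Trajectory at ρ = 0.5, difference only at T2 and T3: 30%, 33% and 44% at N = 67, 74 and 100.
- Trajectory at ρ = 0.5, 3.8 days at T1 and half of that afterwards: 16%, 18% and 23%.

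Overall this is roughly 16 to 53%. Moving both in the favourable direction at once (ρ = 0.7, difference only at T2 and T3, N = 100: λ = (100/4) × 14.44/(11.99² × 0.3) = 8.37) gives 67%, still short of 80%.

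**6. Check that needs neither ρ nor trajectory.** A two-sample t-test on one change score with d = 0.307 gives 24%, 26% and 33% at N = 67, 74 and 100. It needs about 336 patients for 80%.

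**7. Detectable difference.** Solving step 4 for 80% power with a persistent difference and ρ = 0.5 gives 8.0 days (N = 67), 7.6 days (N = 74) and 6.5 days (N = 100).

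**The case against.** The strongest reply is that the calculation was carried out correctly and that the article does not fix what the true power depends on. Both points stand. The sum reproduces, so the fault lies in the effect size supplied. ρ, the trajectory and the covariance structure are not stated, so no single corrected figure can be claimed. But no plausible choice on the article's SDs rescues 80%. The 2 × 4 test would need ρ of about 0.87 at N = 74 or 0.83 at N = 100, against an implied 0.47. A more favourable one-degree-of-freedom contrast of baseline against the mean of the follow-ups reaches only about 36% and 46%.

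A reader might infer more than the article supports:

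- **That entering 3 measurements while analysing 4 causes the shortfall.** It does not. The article explains the 3, and entering 4 with the same f would have asked for fewer patients (62).
- **That the interaction is exactly zero, because a constant difference across three changes is a group main effect.** That holds only if all three are changes from baseline and the difference is constant. The wording also fits successive intervals, and the planned test uses the four time points.
- **That power is lower still because this sample drinks less.** The exclusion of "Current (in the last two weeks before eligibility screening) regular alcohol use" above set weekly limits, and the fact that "All participants already receive TAU at the moment they are enrolled", do suggest lighter drinking at T0. That could shrink the attainable difference, but it could also shrink the SD, which raises power for a fixed 3.8 days. With illustrative SDs of 10, 8 and 7 and ρ = 0.5, step 4 gives 35%, 53% and 66% at N = 74, and 47%, 68% and 80% at N = 100. The article gives no SD for this sample, so the net direction is unknown. The cited baseline mean of 16.33 days is not an input to the calculation.

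**Conclusion.** The point holds as an error of effect-size specification. A between-group f for one change score was used as a within-between interaction f, which roughly doubles f and overstates λ about fourfold. The stated 80% power for 3.8 days with 74 patients does not follow from the article's own figures. The central figures of 23%, 25% and 33% (67, 74 and 100 analysed) rest on SD about 12, ρ = 0.5, compound symmetry and a difference that persists from T1. They should be read within the 16 to 53% range rather than as exact values. The change-score t-test, which relies on none of the trajectory or correlation assumptions, agrees closely. The conclusion is conditional on SDs close to those that the article cites.

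**What to change.** In Power and sample size calculation:

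1. Delete the claim that 74 patients give 80% power for 3.8 days.
2. State the power of the planned 2 × 4 test for 3.8 days with the SD, ρ, trajectory and number analysed all named: about 23%, 25% and 33% for 67, 74 and 100 under the assumptions above, with the range of roughly 16 to 53%.
3. State that 80% power is reached only for a persistent difference of about 6.5 days (100 analysed) to 8.0 days (67 analysed).

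In Analyses, commit to reporting the between-group difference in change in heavy drinking days with its 95% CI, set against 3.8 days, so that a non-significant result is not taken to rule out the target effect.

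The cost is a rewritten paragraph and one added reporting sentence. No extra patients are needed. The downside is that the stated power becomes less favourable.

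### Enrolling 100 does not cover the stated 33% attrition: 67 patients remain, not the required 74

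*Protocol article*

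**What the plan says.** The section on power and sample size in the protocol article makes three linked statements.

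- **Requirement.** A G*Power calculation for the group-by-time interaction in a repeated measures ANOVA "indicated a sample size of 74 to demonstrate this effect". The effect size comes from a difference of 3.8 heavy drinking days, "which corresponds to an effect size of *d* = 0.31 or *f* = 0.15". The article describes the calculation as "keeping α at 0.05 and power at 0.80 and using 2 groups and 3 measurements".
- **Expected loss and enrolment.** "Attrition is estimated to be relatively high at 33%. Therefore we add 26 participants (100 patients in total, 50 in each treatment arm").
- **Claim.** The enlarged total is presented as enough to reach the number that the calculation asks for.

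The Analyses section adds that all allocated participants enter the primary intention-to-treat analysis, with multiple imputation or a similar strategy if possible, and that a completers analysis will also be done.

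**The concern.** Attrition is the share of enrolled patients who are lost, so it has to be taken off the number enrolled. The 26 extra patients are 26% of 100. They cannot replace a loss of 33% of 100. The requirement of 74, the loss of 33% and the claim that 100 is enough cannot all be true.

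At stake is the sample size justification for the primary outcome. If attrition runs as the authors expect, the trial ends below the number they set for themselves, and power falls below their own 80% threshold. The Background faults the one earlier randomised trial for small size and high attrition, so the attrition allowance is central to the case for this trial.

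**Working it through.** **Inputs from the power and sample size section:** f = 0.15, α = 0.05, power 0.80, k = 2 groups, m = 3 measurements, required N = 74, attrition 33%, enrolment 100. **Assumed, because not stated:** correlation between repeated measures ρ = 0.5 and no nonsphericity correction (ε = 1).

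**1. The effect size.** The reductions are 8.7 (SD 12.5, n = 618) and 12.5 (SD 12.2, n = 362). The pooled SD is √[(617 × 12.5² + 361 × 12.2²) / 978] = 12.39. So d = 3.8 / 12.39 = 0.307 and f = d / 2 = 0.153, in line with the stated 0.31 and 0.15.

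**2. The required 74.** For the within-between interaction, λ = f² × N × m / (1 − ρ), with (k − 1)(m − 1) and (N − k)(m − 1) degrees of freedom.

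- At N = 74, λ = 0.0225 × 74 × 3 / 0.5 = 9.99 on 2 and 144 df, and power is 0.806.
- At N = 72, power is 0.795.

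So 74 is the smallest total with equal arms that reaches 0.80, which matches the article.

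**3. The step from 74 to 100.**

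| Calculation | Result |
|---|---|
| Mark-up on the required number: 74 × 1.33 | 98.4, so 99; 100 with arms of 50 |
| Division by the fraction retained: 74 / (1 − 0.33) | 110.4, so 111; 112 with arms of 56 |
| Left after 33% loss from 100: 100 × 0.67 | 67 |
| Shortfall: 74 − 67 | 7 |
| Largest loss that leaves 74 of 100: 26 / 100 | 26% |

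Only the mark-up comes close to the stated 100. The article does not say how 26 was reached, so this is the likely cause and not an established one. The shortfall is the same whatever the cause.

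**4. Power with 67 patients.** At N = 67, λ = 0.0225 × 67 × 3 / 0.5 = 9.045 on 2 and 130 df, and power is 0.763.

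**5. Dependence on ρ.** At m = 3, f = 0.15 and N = 67:

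| ρ | Power at N = 67 | N required for 0.80 |
|---|---|---|
| 0.3 | 0.61 | 102 |
| 0.5 | 0.76 | 74 |
| 0.7 | 0.94 | 46 |

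Of these, only ρ = 0.5 agrees with the stated requirement of 74. The head count of 67 against 74 does not depend on ρ.

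**The case against.** The strongest reply is that the primary analysis is intention-to-treat with imputation, so all 100 patients enter it. On that view 67 is a count of complete cases, and patients who leave late still contribute their earlier assessments. The 76% would then be nearer a complete-case lower figure than the expected power of the primary test. This is fair about the consequence, but it does not save the statement. Imputation is planned only if possible, it does not restore all the information lost, and it does nothing for the completers analysis. The section itself adds patients so that 74 remain after loss.

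A second reply is that the planned analysis has four time points, not three. With m = 4 and the same f and ρ, 62 patients would suffice and power at 67 would be 0.83. So this step alone does not show that the trial is underpowered. But the article bases its requirement on three measurements, and the attrition allowance has to be right for the calculation it reports.

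A third reply is that ρ is not stated, so 76% is not strictly the article's own figure. That is correct: ρ = 0.5 is inferred, and it should be labelled so wherever the 76% is quoted.

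Finally, the effect is small and no more patients are asked for. That bears on how serious the error is, not on whether it is one.

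**Conclusion.** The concern holds. At the stated 33% attrition, 100 enrolled patients leave 67 complete cases, 7 short of the required 74. An enrolment of 100 covers at most 26% attrition, and 33% would require 111 patients, or 112 for equal arms. These results need only the article's own figures, and nothing elsewhere in it corrects them.

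The cost in power is about 4 points: 0.763 against 0.806 at N = 74, and below the 0.80 target. This rests on f = 0.15, three measurements, ρ = 0.5 (inferred from the stated 74), ε = 1 and an analysis of complete cases. The practical loss is modest, and imputation may reduce it. The claim that 100 meets the requirement is still false as written.

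**What to change.** Replace the sentence on the added participants with one along these lines: *With 100 patients randomised, 74 remain if attrition is 26% or less; at the expected 33%, 67 complete cases remain, and power is about 76% (f = 0.15, three measurements, correlation between repeated measures assumed to be 0.5).* The sponsor should confirm the correlation used in G*Power and state it.

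This costs one sentence and a slightly less favourable power figure. Recruitment, randomisation and the analysis stay as they are. Keeping both the 33% and the 74 would instead mean enrolling 111 patients, or 112 for equal arms. That is an option for the sponsor, but it is not needed to make the statement true.

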### Interventions

#### Treatment as usual (TAU)

All participants already receive TAU at the moment they are enrolled and will continue to receive TAU for as long as indicated by their regular therapists but at least until T1. TAU may differ in intensity or additional components delivered (e.g. family treatment) between participants. In IrisZorg, most out-patients of care pathway ‘youth’ and ‘addiction’ receive (Adolescent) Community Reinforcement Approach ((A)CRA) treatment, consisting of several interventions, based on behavioral therapy principles [48]. Elements may include: functional analysis, training communication and/or problem-solving skills, sobriety sampling, social networking, learning to refuse substances, increasing alternative reinforcing activities, relapse management and medication monitoring. Treatment is individual but may also be partly groupwise. Patients receive TAU on a weekly basis by a health care worker.

Alternatively, some patients in care pathway ‘young’ may receive an intensive family treatment for youngsters up to 20 years old (and their families), who still live at home (or intend to go back to live at home again) and where multiple life domains may be affected (e.g. family, school, mental health, criminal behavior etc.): Multidimensional Family Therapy (MDFT [49]). Patients of care pathway ‘addition, care and housing’ receive Function Assertive Community Treatment (FACT [50]), a multidisciplinary, outreaching approach aimed at stabilization, treatment and recovery.

TAU is supervised by a clinical psychologist or psychiatrist. If necessary, treatment may be supplemented with medical care (such as, but not limited to medication), individual psychological care or relationship or family therapy. Incidentally or periodically, additional in-patient treatment may be necessary. CRA and MDFT typically lasts 6 months (in some cases CRA may be limited to 3 or extended to 9 months) while FACT may endure much longer.

‘Time-in-treatment’ before intervention and during the course of the study as well as main components and treatment intensity of TAU will be registered. The use of psychofarmaca, craving reducing (acamprosate, naltrexone) or abstinence enforcing medication (disulfuram) will be monitored.

